### Participants characteristics and eligibility criteria

2.2

Participants meeting the following inclusion criteria will be recruited.1.Highly trained male field football referees registered in the Portuguese Football Federation aged ≥18 and ≤45 years;2.With normal weight (Body Mass Index ≥18.5 and ≤24.9 kg/m^2^);3.Availability to participate in the introductory meeting, familiarization session and 2 experimental sessions;4.Ability to read and agree to sign the informed consent.

Participants with at least one of the following criteria will be excluded from the study.1.Under the influence of any medications that may affect urinary parameters, thermoregulation mechanisms, circulatory system, thyroid and pituitary function or metabolic status;2.Injury, diabetes, autoimmune disease, cardiovascular disease or obstructive disease of the gastrointestinal tract (e.g., diverticulitis, inflammatory bowel disease);3.Schizophrenia, bipolar disorder or other psychotic disorders;4.Diagnosed eating disorders;5.Magnetic resonance imaging (MRI) scans performed within 48 h after familiarization session or any of the experimental trials.

### Study design, setting and randomization

2.3

A randomized counterbalanced crossover trial with two conditions will be carried out. After passing the eligibility criteria and attending the introductory meeting and a familiarization visit, the participants will be assigned to 2 experimental days for undergoing 2 different randomly ordered experimental conditions. Each condition will be comprised of a 90-min football protocol (SAFT 90) [31], with the administration of one of 2 beverages before warm-up (5 min of pre-cooling) and at the half-time (5 min of per-cooling). There will be a minimum washout period of 7 days between each trial, to reduce carryover effects from the previous condition and to assure an adequate exercise recovery. The trials will take place in an indoor environment, with Wet Bulb Globe Temperature (WBGT) values exceeding 30 °C, at the same time of the day, to control for circadian variations.

After the familiarization visit, the allocation sequence for the order of the experimental conditions will be assigned through individual randomization from a computer-generated random order, equally assigned to every participant, by the main researcher. Randomization will be concealed through a password-protected document that will not be revealed until the first trial. The main researcher will not be blinded in this type of study condition and will have access to the allocation sequence list and will retrieve the randomization code prior to each experimental to prepare the beverages. All the other investigators and the outcomes assessors will be blinded to study condition and group allocation, as well as participants will be blind to the beverages content and aim of the study.

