**Methods:**

At least thirteen male football referees will be recruited to perform two intermittent football protocols, separated by no less than 7 days. After passing the eligibility criteria, the participants will be randomly assigned to 1 of 2 beverages: (1) intervention - menthol solution 0.01% and (2) placebo - noncaloric berry-flavored solution, both at room temperature. The beverages will be given before warm-up (pre-cooling) and at the half-time (per-cooling). The trials will follow a randomized counterbalanced crossover design, single blinded, and will take place in indoor facilities, with Wet Bulb Globe Temperature (WBGT) > 30 °C, at the same time of the day to control for circadian variations.

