### Sample size and recruitment

2.1

For sample size and statistical power calculations, power analysis was based on changes in TS after the internal administration via mouth-rinsing or ingestion of menthol solution. Considering a type I error of 5% and a power of 90%, with a statistical significance (p-value ≤0.05) and a moderate effect size of 0.54 (differences in TS were considered following Jeffries and Waldron results [30]), a total of 10 participants will be needed (using G*Power 3.1.9.2 ®). Considering a drop-out rate of 30% throughout the study, 13 participants as a buffer against attrition.

The Portuguese Football Federation (PFF) will contribute by recruiting referees through direct contact, databases, and referral sources. Following an initial telephone screen to determine the eligibility of potential participants, an orientation session (introductory meeting) will be scheduled to offer detailed information about the study, including the number and type of assessments, the length and nature of the exercise training, and the time commitment required to complete the study. After eligibility criteria confirmation, all participants will sign an informed consent form before being allocated to the study. Participants’ privacy and confidentiality will be guaranteed during and after investigation according to the Portuguese data protection law. Privacy, anonymity, and confidentiality of data/information identifying the participants will be strictly maintained. All information and results of the tests performed on the participants will be confidential. No one other than the investigators of this research will have access to the data.

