Mouth-rinsing a menthol solution throughout exercise has shown to improve time to exhaustion [[50], [51], [52], [53]], power output [50,52,54], completion time in a time trial [54,55] in other studies in laboratory context within a different range of participants. As such, we posit that menthol will also benefit sports performance in an intermittent protocol with elite referees. Additionally, TS [50,52] and comfort rating scales [50], and physiological strain [53,55] are also expected to improve compared to the exercise under the same conditions without any cooling strategy, as other studies suggest.

Oral menthol administration has been more frequently investigated as a per-cooling technique. Most studies assumed that this method will only have an ergogenic effect if applied during more advanced stages of exercise. However, in one study, the authors opted to apply menthol mouth rinsing 1 min before the start of a 3-min aerobic test, and found significant improvements in physical performance [56]. While in internal thermal cooling methods, it is important that pre-cooling is carried out in advance to see improvements in heat storage, in the case of menthol it seems that pre-cooling can be performed very shortly before the start of the protocol [56]. This increases the likelihood of immediately improving the TS and TC in the initial phases of short exercises. So, for those reasons, a pre- and per-cooling mode will be chosen to administrate oral menthol to the referees in the current research protocol. This way, we will be able to understand the effects of menthol even at the earliest stages of exercise.

The main strength of the present study is the design. By using a crossover trial to compare the interventions, we can minimize the risk of confounding because each participant will be their own control. On the other hand, counterbalancing will allow to control the effects of nuisance variables (e.g., small differences on ambient conditions between the trials, acclimatization effect, and beverages selection order bias), thus enhancing the study's interval validity.

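### The stated analysis has no period term, so protection against acclimatisation and order effects rests on equal sequences, which the planned drop-out and exclusions would often break

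*Protocol article*

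**What the plan says.** - **Design (Section 2.3):** "A randomized counterbalanced crossover trial with two conditions will be carried out". Order comes from "individual randomization from a computer-generated random order, equally assigned to every participant". The section also mentions an allocation list, held in a protected file. It names no block, fixed list or other restriction.
- **Role of balance (Discussion):** "counterbalancing will allow to control the effects of nuisance variables". The examples given are small ambient differences between trials, acclimatisation and order of beverages. The crossover design is presented as the study's main strength.
- **Numbers (Section 2.1 and abstract):** "a total of 10 participants will be needed", and "Considering a drop-out rate of 30% throughout the study, 13 participants as a buffer against attrition". The abstract words the target as a minimum: "At least thirteen male football referees will be recruited to perform two intermittent football protocols".
- **Analysis (Section 2.7):** a one-way repeated-measures ANOVA relates the intervention to the responses, a one-way ANOVA handles single time-point data, and a two-way repeated-measures ANOVA covers time in both conditions. Time here means time within a session. No period or sequence term appears. Missing data are left out, and the section excludes participants who discontinue or depart from the intervention protocol.
- **Acclimatisation (Section 2.4.5):** conditions on the two days before each test are recorded because acclimatisation might affect the results.

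**The concern.** In a two-period crossover, equal sequence sizes cancel a period effect from the simple menthol-minus-placebo difference. A period term in the model removes it whatever the sizes. The article relies on the first route only. That route needs balance among the participants actually analysed, not just on the randomisation list. The plan itself expects 30% drop-out and removes those who discontinue or deviate, so balance at the start need not survive to the analysis.

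At stake is the main comparison in about 10 people. With unequal sequences, part of any difference between session 1 and session 2 is read as a menthol effect, or masks one. With nearly equal sequences, the period effect goes into the residual variance and the test loses power.

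**Working it through.** **Inputs.** From Section 2.1: 10 needed, 30% drop-out, 13 recruited. From Section 2.7: no period term. Assumptions: a balanced 7:6 list, loss unrelated to sequence, and a period effect π of 0.25 to 1.0 SD of the within-person difference, because the documents give no size.

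**The plan's own figure.** 10 × 1.30 = 13, so the target is reproduced, and a loss of 3 leaves the 10 that are needed. Applying 30% to 13 gives 3.9 lost, so a loss of 3 is slightly milder than the stated rate.

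**Leak.** Let τ be the menthol effect and π the session 1 minus session 2 effect. The menthol-minus-placebo difference has mean τ + π in the menthol-first sequence (n1 people) and τ − π in the other (n2). The unadjusted mean is τ + π(n1 − n2)/N. The plain average of the two sequence means is τ at any split; this is what a period term delivers.

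**Loss of 3 from a 7:6 list.** There are C(13,3) = 286 equally likely sets.

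| Lost from the 7 / from the 6 | Sets | Remaining split | Share of π that enters |
|---|---|---|---|
| 2 / 1 | 21 × 6 = 126 | 5:5 | 0 |
| 1 / 2 or 3 / 0 | 7 × 15 + 35 = 140 | 6:4 (either way) | 2/10 = 20% |
| 0 / 3 | 20 | 7:3 | 4/10 = 40% |

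Equal: 126/286 = 44%. Unequal: 160/286 = 56%, made up of 140/286 = 49% and 20/286 = 7%. If 4 are lost, the 9 who remain cannot split equally, and at least 1/9 = 11% of π enters.

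**Size of the shift.** At 6:4: 0.20 × 0.25 = 0.05 SD to 0.20 × 1.0 = 0.20 SD. At 7:3: 0.40 × 0.25 = 0.10 SD to 0.40 × 1.0 = 0.40 SD.

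**Near balance.** Without a period term, the expected residual variance (in units of the true variance) is 1 + π² × 4·n1·n2/[N(N − 1)]. At 7:6 the multiplier of π² is 4 × 42/(13 × 12) = 1.077, so the variance rises by 7% at π = 0.25, 31% at 0.54 and 108% at 1.0. In simulation (unadjusted paired t-test, 200,000 runs per scenario, nominal 5%), type I error at 7:6 was 4.4%, 2.8% and 0.8% respectively. The test is conservative, which means lost power.

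**Cost of the period term.** The variance factor is (N/4)(1/n1 + 1/n2): 169/168 = 1.006 at 7:6, 169/160 = 1.056 at 8:5 and 169/144 = 1.174 at 9:4.

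**If the list were unrestricted (binomial, N = 13).** P(7:6) = 2 × 1716/8192 = 41.9%, so 8:5 or worse has probability 58.1%. P(8:5) = 2 × 1287/8192 = 31.4%, so 9:4 or worse has 26.7%. At 9:4, 5/13 = 38% of π enters.

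**The case against.** A reader might infer that order is assigned by unrestricted coin-toss, contradicting the counterbalanced label. The text does not establish this. Individual names the unit randomised, a blocked list is also individual randomisation, and the wording about equal assignment together with a prepared list fits a balanced scheme. A journal article may also leave block details to the full protocol. This is an ambiguity, and the 58% and 27% figures apply only if the list is in fact unrestricted.

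A reader might also blame the odd number. On its own, 13 forces only 7:6, a leak of 1/13 = 7.7%, and the abstract makes 13 a minimum.

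Nor is the leak a systematic bias. When either sequence is equally likely to be the larger, it averages to zero; under simple randomisation at 13 the simulated type I error was 5.0% to 5.1% for period effects of 0.25 to 1.0 SD. The problem lies in the one split that occurs. Learning from a repeated exercise test is a weaker source than acclimatisation, because everyone has a familiarisation session and audio signals control the activity.

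Finally, a separate analysis plan could contain a period term. That possibility stands. But Section 2.7 is not silent on the model: it names the analyses, and the Discussion assigns control of these nuisances to counterbalancing. As stated, nothing adjusts for sequences left unequal by drop-out or exclusion.

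**Conclusion.** The point holds for the analysis model. Even granting a balanced list, sequences would end unequal about 56% of the time after a random loss of 3 of 13, with 20% or 40% of any period effect entering the realised contrast. Where sequences stay near equal, omitting period costs power instead. This rests on loss unrelated to sequence and on a period effect whose size the documents do not give; if it is negligible, so is the harm. The allocation wording needs clarifying but is not shown to be wrong. The change is worth making because it is cheap and secures the protection that the Discussion claims.

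**What to change.** 1. **Section 2.7:** analyse the condition contrast with period as a fixed effect, for example a mixed model with condition, period and participant, or the equivalent paired comparison adjusted for sequence. Add period in the same way to the analysis of time within session. This is the more important change, because it covers imbalance from allocation, drop-out and exclusions alike.
2. **Section 2.3:** state that the computer-generated list is balanced by sequence, using permuted blocks. If the list is in fact unrestricted, say so and rely on the period term.

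Cost: a few words in each section, one degree of freedom, and a variance increase of 0.6% at 7:6, 5.6% at 8:5 or 17% at 9:4. Very small blocks would make the order more predictable to the main researcher, who is already unblinded and holds the list.

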### Data management

2.5

All participants will be assigned a unique identifier to protect they identify. All personal data will be stored in encrypted files with access restricted to the main researcher. Original paper files will be stored in secure, locked cabinets onsite. All data will be inserted electronically. Data will be double-checked for errors at the time of entry, with all changes performed being documented. Additional findings will be performed through statistical software. Data ranges and consistency checks will be performed for data integrity. No specific auditing procedures are planned for this trial. The results will be fully disseminated in peer-reviewed scientific journals and conferences.

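### The unblinded main researcher assigns the beverage order and has access to the list, so the password-protected file does not secure concealment from the person making the assignments

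*Protocol article*

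**What the plan says.** All the relevant statements on allocation are in section 2.3 (Study design, setting and randomization) of the protocol article.

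- **Assignment.** Once the familiarization visit is over, the order of conditions is "assigned through individual randomization from a computer-generated random order, equally assigned to every participant, by the main researcher".
- **Concealment.** "Randomization will be concealed through a password-protected document that will not be revealed until the first trial".
- **Access and use.** The main researcher "will have access to the allocation sequence list and will retrieve the randomization code prior to each experimental to prepare the beverages".
- **Blinding.** "The main researcher will not be blinded in this type of study condition", whereas "All the other investigators and the outcomes assessors will be blinded to study condition and group allocation". Participants are also to be kept unaware of the beverage content and the aim of the study.

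Section 2.1 (Sample size and recruitment) puts confirmation of eligibility and signed consent before allocation, and gives the national federation a part in recruiting. No separate holder of the list is named.

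**The concern.** Allocation concealment exists to keep an upcoming assignment from the person who makes it. Here that person has access to the list, so the stated mechanism and the stated division of roles do not fit together.

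The crossover design narrows the issue without removing it. Suppose menthol has no effect. A referee who takes placebo first then shows a menthol-minus-placebo difference equal to his session-2-minus-session-1 change, and a referee who takes menthol first shows the negative of his. These changes cancel on average only if order is independent of each referee's own change. The article relies on this: its Discussion credits counterbalancing with controlling small ambient differences, acclimatization and order effects, and section 2.4.5 records weather on the two preceding days because acclimatization might interfere. If order could be matched to the referee, part of the period change could be credited to a beverage. Equal numbers per order would not prevent that, because the bias comes from who is in each order.

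**Working it through.** **Step 1: who can see the order.** The article gives no figure on this point to reproduce, so this step sets its statements side by side.

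| Role | Stated position | Does the password file conceal the order? |
|---|---|---|
| Participants | blinded to content and aim | It can |
| Other investigators, assessors | blinded to condition and allocation | It can |
| Main researcher | assigns order, has list access, retrieves codes, unblinded | Not secured |

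**Step 2: what could be influenced.** Eligibility and consent come first, so foreknowledge has little room to affect entry. Both rinses are given to everyone, so it cannot affect which treatment a referee receives. What remains is which referee gets which order, and when sessions are booked.

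**Step 3: how much steering of order would matter.** This is an illustration on assumptions.

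Inputs: N = 13 (section 2.1). Assumed: orders split 7:6; no menthol effect; individual session-2-minus-session-1 change g standard normal, so the unit is the SD of that change; a prediction of g with correlation r; two-sided 5% tests.

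Model: the menthol-minus-placebo difference is d = s × g, with s = +1 for placebo first and −1 for menthol first. The plain test is a paired t-test on d. The period-adjusted test compares mean g between the two orders.

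Under full sorting, the seven referees with the highest predicted change all get placebo first. The expected bias is then

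bias = r × (2/13) × (sum of the six largest expected normal order statistics for n = 13)

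= r × (2/13) × (1.668 + 1.164 + 0.850 + 0.603 + 0.388 + 0.190)

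= r × (2/13) × 4.863 = 0.748 r.

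Type I error by simulation (200,000 trials per setting):

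| r | Bias, full sorting (SD) | Paired test, full sorting | Period-adjusted, full sorting | Paired test, one pair swapped |
|---|---|---|---|---|
| 0 | 0.00 | 5.0% | 5.0% | 5.0% |
| 0.1 | 0.07 | 5.7% | 5.8% | 5.2% |
| 0.2 | 0.15 | 8.0% | 8.0% | 5.7% |
| 0.3 | 0.22 | 12.0% | 11.9% | 6.8% |
| 0.5 | 0.37 | 26.4% | 26.6% | 9.9% |

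The last column starts from a random 7:6 list and exchanges only the two referees whose swap fits the prediction best. When the random list is followed as it stands, bias is zero and type I error is 5% whatever r is. Shorter runs of 20,000 trials put full sorting at r = 0.3 between 11% and 12%. A period term does not repair the problem, because it removes the average period change and not its link with order.

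**The case against.** The case against making much of this is strong on several counts.

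- A reader might infer that the main researcher generates the list and knows every assignment in advance. The article says only that the order is computer-generated and assigned by that role, and that the file stays closed until the first trial. It does not say when the main researcher first opens it. The wording permits advance knowledge but does not establish it.
- A reader might infer that there is no concealment at all. That goes too far, because the file can still hide the order from everyone else, and those people are stated to be blinded.
- The usual harm of failed concealment, selective entry, is largely closed off by consent before allocation and by both rinses being given to all.
- Full sorting describes deliberate disregard of the random list. Nothing in the article suggests it, and no value of r can be drawn from it. One familiarization session does not show a session-1-to-session-2 change, and it should reduce learning effects.
- It is tempting to add that the main researcher alone controls the personal data or decides who has deviated. The data restriction in section 2.5 is a confidentiality measure, and section 2.7 does not say who judges deviations, so neither supports the point.
- The bias should not be set against the effect size of 0.54 in section 2.1, whose test and metric are not given.

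All of this stands, and it limits the size of the point. It does not remove the mismatch itself. The article states both the concealment mechanism and the roles, so this is not detail lost in condensing a longer protocol.

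**Conclusion.** The point holds in a limited form. As written, section 2.3 does not secure concealment of the order from the unblinded person who assigns it, though it can secure it from participants, other investigators and assessors. The exposure is confined to which referee gets which order and to session booking.

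The effect is nil with honest use of the list and small with weak steering: type I error stays below 6% at r = 0.1 even under full sorting, and below 7% at r = 0.3 with one pair swapped. It reaches about 11–12% only with full sorting at r = 0.3, and about 26% at r = 0.5. Those r values, the 7:6 split and the normal model are assumptions. No misconduct is alleged. The weakness is that the stated procedure does not exclude steering, and neither counterbalancing nor a period term would correct it afterwards.

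**What to change.** Keep the computer-generated list and the password-protected file, and change section 2.3 as follows:

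1. Fix and record participant numbers in order of consent, before the list is generated.
2. Have an existing faculty colleague with no participant contact generate the list and hold the password. The federation is not suitable, because it recruits the referees.
3. Release each participant's order to the main researcher only after that participant's sessions are booked and when the first beverage has to be prepared.

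The main researcher can still prepare the beverages unblinded. The cost is a few sentences in 2.3 and one message per participant, with no extra visits, participants or staff post. The one drawback is that the list holder must be reachable before each first session. The article says the trial is not yet under way, so the change can be made before anyone is assigned.
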